## Abstract

**Background:**

Studies have shown that university/college students tend to have an exaggerated view of the quantities of alcohol being consumed by their peers. Making students aware of this misperception may help change behaviour and reduce problem drinking.

**Methods/Design:**

A Solomon Three Group Design will be used. There is one intervention group and two control groups, controlling separately for measurement and for intervention effects. Recruitment, consent, randomisation and data collection are all on-line. The primary outcomes are AUDIT Score, weekly consumption, perceived social norms, and alcohol related problems; secondary outcomes include alcohol expectancies and other health behaviours.

**Discussion:**

This trial will provide information on the effectiveness of an on-line personalized normative feedback intervention for alcohol misuse in university students.

**Trial registration:**

International Standard Randomised Controlled Trial Number: ISRCTN30784467

## Background

### Alcohol related problems

Around 55,000 young people in Europe died from causes related to alcohol use in 1999 [1,2]. In the UK alcohol-related mortality is increasing compared with many other European countries where rates are declining or unchanged. At the same time, binge drinking rates amongst young people are high in the UK and Holland, and are increasing in the UK where alcohol related violence and crime is a major cause for concern. Therefore an effective prevention programme that has a significant impact on alcohol related problems amongst young people would be very important.

### Normative feedback

Normative feedback as an approach to alcohol misuse prevention is based on Social Norming Theory. Initially developed in the United States, this approach relies on changing the attitudes and norms that exist around drinking behaviours, typically on University campuses. The normative feedback approach relies largely on raising awareness amongst students about how much their peers actually drink (and do not drink) and to correct existing misperceptions [3]. Information about how much students actually consume, accurate statistics about the frequency of negative consequences among them and basic information relating to alcohol are part of the approach [4]. Currently there is no published Cochrane systematic review on the effectiveness of social norms approaches, though a Cochrane protocol on this topic has been published [5]. One of the best trials we have identified so far has been by Kypri [6]in New Zealand, where an electronic Screening and Brief Intervention (SBI) approach identified students at high risk and then provided normative feedback to this group. After 12 months this group had significantly lower alcohol-related problem scores than controls. However, Kypri has not been able to establish whether the normative feedback intervention, or simply measuring drinking behaviour using the alcohol use disorders identification test (AUDIT) screening tool, was the active ingredient accounting for this effect. Kypri also suggested that a social desirability response bias may have influenced the results.

### Potential population impact

Working with Kypri, we have used his dataset to model the potential of normative feedback to reduce alcohol related problems. Using a Bayesian approach [7], we have estimated that the change in alcohol related problem scores from Kypri's study might equate to a 5% prevalence reduction in alcohol disorders (DSM dependence and abuse), which would be a marked and important consequence [8]. We have not been able to assess impact on acute harms, violence and crime because of insufficient information for modelling. We are also interested in how the prevention paradox should inform the choice of intervention population. Although Kypri [9] and others have targeted high risk drinkers, the prevention paradox states that more harm comes from those at lower levels of risk, and Rossow [10] has recently demonstrated that this paradox holds, albeit to a lesser extent, for heavy episodic drinking and acute harms. Therefore it is possible that this relatively cheap intervention may be relatively more effective if delivered at a whole population level rather than just to those at higher levels of risk.

## Methods/Design

### Aims of the project

The aim of the trial is to determine the effectiveness of an on-line personalized feedback intervention for reducing alcohol consumption amongst undergraduate University students when compared with a control group, in both the UK and Portugal.

The objectives of this trial are:

• To examine the effectiveness of brief personalized normative feedback in reducing alcohol related problems in first and second year university undergraduate students

• To compare the effectiveness of brief personalized normative feedback between students in England and students in Portugal

• To assess the relative effectiveness of whole population (universal) versus screening and brief intervention (SBI; targeted) normative feedback in reducing alcohol related problems.

### Design

A Solomon Three Group Design [11] will be used in each country (UK and Portugal) where participants will be randomly assigned, with concealed allocation, to one of three groups (see Figure 1). Baseline alcohol use and misuse will be measured in two of the groups, but not the third group. Demographic questions will be answered by all three groups before randomization. There is one intervention group and two control groups, controlling separately for measurement and for intervention effects. The intervention group will receive the brief personalized normative feedback via email within a few weeks of completing the assessment and will be followed up at 6 months, along with the first control group. All three groups will be followed up at 12 months.

**Figure 1 F1:**
[figure not shown]
Solomon Three Group design (for each country).

### Ethics

Ethics approval for this study is provided by Oxford Brookes University Research Ethics Committee (REC No-2006/28).

### Setting and participants

Participants are undergraduate university students (first and second year) enrolled in UK and Portuguese universities.

### Recruitment

Undergraduate students in year one and two of their course will be invited to participate via poster, flyer, email or via university student information systems at the beginning of the academic year 2007/8. Oxford, Oxford Brookes, Nottingham and Plymouth Universities in the UK and Portucalense, Lusiada, Fernando Pessoa, Autonoma and ISMAI Universities from Portugal have agreed to collaborate. Furthermore, students will also be recruited via Facebook, a social networking website.

### Randomisation

Randomisation occurs after students have read the consent form, with affirmative consent given proceeding to the on-line questionnaire. At this point, participants are randomised to intervention or control groups. Randomisation is achieved by concealed centrally-allocated computer generated random numbers.

### Intervention

The brief personalised normative feedback given to each intervention group participant will comprise the results of their drinking behaviour assessment alongside information about alcohol and how it might affect them at their current drinking levels. The feedback will also compare their drinking – in graphical format – to the drinking of their student peers. Information will also be provided on the money that they might be spending on alcohol and also the calories they might be consuming at their current drinking levels. Details of sensible drinking levels will also be provided and contact details of health services and helplines they can contact if they feel they need further help.

### Outcome measures

Alongside demographic questions (including: age, gender, weight, nationality, university year) we have carefully selected validated measurement instruments:

• Alcohol Use Disorders Inventory Test (AUDIT) and brief version (AUDIT-C)

• Alcohol Expectancies Questionnaire (AEQ, brief version)

• Social Desirability Scale (SDS, brief version)

• Self-report measures on alcohol consumption (from ESPAD and Centre for Addiction and Mental Health (CAMH), Toronto) [12,13]

• Perceived norms (validated adaptation of the two versions of the Drinking Norms Rating Form)

### Data collection

Data are collected at baseline, six months and 12 months. All data collection is done online, through the trial website, accessed via a web-link promoted in all forms of advertisement.

A further methodological challenge is the expected high rate of attrition from follow-up. We have incorporated a number of features designed to improve this, including:

• Three e-mail reminders at seven day intervals to non-responders;

• The use of an appropriate incentive;

• Assurance of confidentiality.

### Sample size calculation

A figure of 150 students per group is specified for analysis for both male and female hazardous drinkers resulting in an overall sample size requirement of 4000 students in each country. We intend to assess intervention efficacy in the student population as a whole and in particular a subgroup of hazardous drinkers (AUDIT ≥ 8), for both males and females. This group is likely to be a minority so the sample size has to be increased to ensure sufficient numbers of this high risk group to enable robust statistical analysis with power =.9 and α = .05 (2-tailed tests) and taking account of expected participation and attrition rates.

### Analyses

Statistical tests of difference in proportions or mean difference tests (or non-parametric equivalents) will be used to test differences between intervention and control groups. Multivariate analyses will be conducted with gender, nationality, University year (one and two), social desirability and study country as covariates. Data will be analysed by a researcher blinded to experimental group.

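### The stated covariate list leaves out the baseline value of the outcome, although baseline drinking is collected in both the intervention and first control groups

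*Protocol article*

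**What the plan says.** The Analyses section of the protocol article describes the between-group tests: "Statistical tests of difference in proportions or mean difference tests (or non-parametric equivalents) will be used to test differences between intervention and control groups". It then names the adjustment variables: "Multivariate analyses will be conducted with gender, nationality, University year (one and two), social desirability and study country as covariates". The list has no opening such as 'for example', and the baseline outcome is not on it. Baseline adjustment, change scores and repeated-measures models are not mentioned anywhere in the article.

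On data availability, the Design section says: "Baseline alcohol use and misuse will be measured in two of the groups, but not the third group". It does not name the two groups, but only one reading fits. The intervention group receives its feedback after completing the assessment, and it "will be followed up at 6 months, along with the first control group". The third group is the unmeasured control. The Design section adds: "All three groups will be followed up at 12 months". All three groups answer demographic questions before randomisation.

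The Abstract lists the outcomes: "The primary outcomes are AUDIT Score, weekly consumption, perceived social norms, and alcohol related problems".

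**The concern.** An earlier measurement of the same outcome is usually among the most informative covariates in a comparison of follow-up values. Here it is collected in both arms of the contrast that isolates feedback from measurement, and it is collected before feedback is sent. The plan names five adjustment variables and passes over this one.

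Two things are at stake for intervention versus first control. The first is precision: leaving baseline out makes the standard error larger than the collected data require. The second concerns follow-up. The Data collection section expects heavy attrition, so those analysed at follow-up may no longer be balanced on baseline drinking. An analysis without baseline carries any such imbalance into the estimated effect.

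**Working it through.** **Inputs from the protocol article (Sample size calculation):** 150 per group ("A figure of 150 students per group is specified for analysis for both male and female hazardous drinkers"), power 0.90, two-sided α 0.05, subgroup AUDIT ≥ 8.

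**Inputs not in the document, so assumed:** the baseline-to-follow-up correlation r, the share of students with AUDIT ≥ 8, and the variance already explained by the listed covariates.

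**Step 1: what 150 per group implies.** The article gives no effect size, standard deviation, prevalence or attrition rate, so 150 and 4000 cannot be reproduced. The standardised difference can be back-solved:

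d = (1.960 + 1.282) × √(2/150) = 0.374.

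**Step 2: gain from adjusting for baseline, no selection on baseline.** Residual variance is multiplied by 1 − r², the standard error and the detectable d by √(1 − r²), and the number needed per group is 150 × (1 − r²). Power at d = 0.374 is Φ(3.242/√(1 − r²) − 1.960).

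| assumed r | variance removed | SE smaller by | detectable d | power at 150 per group |
|---|---|---|---|---|
| 0 (baseline omitted) | 0% | 0% | 0.374 | 90% |
| 0.3 | 9% | 4.6% | 0.357 | 92.5% |
| 0.4 | 16% | 8.3% | 0.343 | 94.3% |
| 0.5 | 25% | 13.4% | 0.324 | 96.3% |
| 0.6 | 36% | 20.0% | 0.299 | 98.2% |
| 0.7 | 49% | 28.6% | 0.267 | 99.5% |

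In sample-size terms, 150 per group falls to 137 at r = 0.3, 113 at r = 0.5 and 77 at r = 0.7 for the same 90% power.

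**Step 3: the AUDIT ≥ 8 subgroup.** The 150 per group are hazardous drinkers. Selecting on baseline AUDIT narrows its range and weakens its correlation with follow-up. A bivariate normal simulation (2,000,000 draws), keeping the top 30%, 40% or 50% on baseline, gave:

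| whole-population r | r within subgroup (30 / 40 / 50% hazardous) | variance removed |
|---|---|---|
| 0.5 | 0.287 / 0.309 / 0.331 | 8.2 / 9.5 / 10.9% |
| 0.6 | 0.361 / 0.387 / 0.413 | 13.1 / 15.0 / 17.0% |
| 0.7 | 0.450 / 0.479 / 0.508 | 20.3 / 23.0 / 25.8% |

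Power at the two ends:
- Low: 3.242/√0.918 − 1.960 = 1.42, so about 92%.
- High: 3.242/√0.742 − 1.960 = 1.80, so about 96%.

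This applies to baseline AUDIT itself. An outcome less closely tied to the selection variable would lose less of its own baseline correlation.

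**Step 4: do the listed covariates already capture this?** Suppose they correlate g with both baseline and follow-up. The partial correlation is then (r − g²)/(1 − g²). For g from 0.1 to 0.3, the 25–49% of Step 2 (r = 0.5 to 0.7) becomes about 20–49%. At r = 0.3 and g = 0.3 it is 0.21/0.91 = 0.231, or about 5%. The gain shrinks but stays positive.

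**Step 5: where adjustment is possible.** Intervention versus first control: baseline alcohol use and misuse exist in both arms. Any contrast with the third group: no individual baseline alcohol measure exists, so only the demographics asked before randomisation can be used.

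**The case against.** The strongest reply is that the Analyses section is three sentences in a condensed article. It does not say that its covariates are the only ones or that they define the primary model, and a fuller plan may adjust for baseline. There is also a design reason for the list: a single model covering all three groups cannot include a baseline alcohol measure that one group lacks, whereas demographics exist for everyone. The article names no main contrast, and contrasts with the unmeasured group are central to its question about measurement effects.

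Part of this stands. The fix reaches only one contrast and requires different covariate sets for different contrasts. But the article names its covariates without qualification, so this is a stated choice and not a detail left open.

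Several stronger readings are tempting, and the document does not support them:
- **That a quarter to a half of the precision is lost.** That is a variance figure under r = 0.5 to 0.7. No correlation is given, the standard error changes by only 13–29% over that range, and the figure is too high for the AUDIT ≥ 8 subgroup.
- **That the omission biases the trial.** Chance imbalance adds variance to a randomised comparison; it does not bias it.
- **That baseline drinking is the strongest predictor of dropout.** The article expects high attrition but says nothing about who leaves.
- **That the non-parametric option is a data-driven switch, or that it removes a mean difference needed for population modelling.** No switching rule is stated. The modelling in the Background used an earlier trial's data, and nothing says this trial's estimates will feed it.
- **That perceived norms are measured at baseline in both groups.** The Design section speaks only of alcohol use and misuse.

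**Conclusion.** The point holds for intervention versus first control: the stated adjustment leaves out a baseline measure that is collected in both arms. It is a worthwhile improvement to the analysis. It is not a flaw that invalidates the comparison.

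The size cannot be fixed from the document. The 9–49% of variance, with power of about 92.5–99.5%, rests on an assumed r of 0.3–0.7 and no selection on baseline. For the hazardous drinkers who drive the sample size, about 8–26% and power of about 92–96% is the more relevant range. It rests on a whole-population r of 0.5–0.7 and 30–50% hazardous drinkers, both assumed. All power figures use d = 0.374, which is back-solved and not stated by the trial.

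The benefit under attrition is conditional: adjustment reduces imbalance among responders only so far as dropout depends on the baseline drinking that was measured.

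**What to change.** For intervention versus first control, add the baseline value of the same outcome to the covariates already listed, in an ANCOVA-type regression of the follow-up value, wherever that outcome was measured at baseline. For contrasts with the unmeasured third group, adjust only for the demographics collected before randomisation. State both covariate sets before the data are analysed, and make clear which contrast uses which. If the expected gain is quoted, give it as r² over a stated range of r, with the smaller figure for the AUDIT ≥ 8 subgroup.

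The change is to wording and needs no new data. Its price is that contrasts involving the third group use a different covariate set from the contrast between the two measured groups.

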## Discussion

This on-line randomised controlled trial has the potential to address three key issues. Firstly, evidence of the potential to reduce hazardous and harmful drinking amongst University students might lead to better prevention programmes across Europe. Second, evidence regarding the differential effectiveness of social norms interventions in countries with different drinking cultures and patterns. And last, evidence about whether universal or targeted approaches are better with this population group.

## List of abbreviations used

AUDIT Alcohol Use Disorders Identification Test

RCT Randomised Controlled Trial

UK United Kingdom

ESPAD European School Survey Project on Alcohol and Other Drugs

CAMH Centre for Addiction and Mental Health

SDS Social Desirability Scale

AEQ Alcohol Expectancies Questionnaire

SBI Screening and Brief Intervention

DSM Diagnostic and Statistical Manual of Mental Disorders
